**4.2 INCLUSION CRITERIA**

**Subjects for enrolment in the study must meet the following criteria:**

- - 1. Subjects must give their signed and dated written informed consent
    2. Subjects must be aged >40 and ≤ 85

**COPD Cohort:**

Subjects with a FEV/FVC <70%

Subjects with a smoking history > 10 pack years. Ex-smokers.

**Healthy Ex-smoker Controls**:

Subjects must have a FEV1/FVC >70%;

Patient and control group will be matched for smoking history and age.

**4.3 EXCLUSION CRITERIA**

Subjects meeting any of the following criteria must not be enrolled in the study:

Resting oxygen saturations <92% on room air.

Long term oxygen therapy

Recent exacerbation of COPD (4 weeks)

Ischaemic heart disease

Cerebrovascular disease

Uncontrolled hypertension

Diabetes mellitus

Hepatic failure

Neurological disease

Non-cured tumours

Obstructive sleep apnoea

Current of past alcohol/drug abuse

Known history of dementia

Visual or hearing impairment that precludes neuropsychological assessment

Neuropsychological tests undertaken outside the study

Pregnant women or women who are lactating

Known alpha 1 anti-trypsin deficiency as a cause of their COPD

History of psychiatric disorders, or other conditions that will impact on the validity of their consent or interfere with compliance to perform study procedures.

Contra indication to MRI scanning

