In addition to cerebral small vessel damage and cognitive dysfunction, other organs such as the heart, kidneys, and retinal are likely to be susceptible to small-vessel damage in COPD. Several large population studies have shown that COPD is a significant independent risk factor for myocardial infarction, with the effect most marked in early, mild disease and that people diagnosed and treated COPD are at increased risk for hospitalizations and deaths due to cardiovascular diseases . Acute exacerbations of COPD are inflammatory episodes associated with platelet activation, troponin rise and subsequent increased cardiovascular events . Left ventricular mass predicts heart failure and cardiovascular mortality and has been found to be increased in COPD and associated with pulmonary hyperinflation . A small exploratory study suggests that occult myocardial infarction may be responsible for delayed cardiac MR enhancement in COPD , another suggests right ventricular hypertrophy on cardiac MR is and early sign of RV overload . Finally percentage of emphysema and lung function have been found to be inversely associated with left ventricular filling, reduced stroke volume and cardiac output with preservation of ejection fraction .

Chronic renal failure is highly prevalent in elderly patients with COPD and associated with systemic inflammation but is a relatively understudied co-morbidity. Micro-albuminuria has been shown to be an independent predictor of future cardiovascular events and a marker of vascular endothelial dysfunction . To our knowledge, retinal vessels have not been extensively investigated in patients with COPD. Retinal photography is a sensitive and precise method of assessing retinal microvascular signs and is thought to be a potential marker for concomitant cerebral microangiopathy. Population based studies indicate that retinal microvascular changes, when defined from photographs, are associated with stroke independent of hypertension may be useful for studying subclinical cerebrovascular disease .

We propose to compare non-invasive MR brain imaging of white matter microstructure (diffusion tensor), cerebral perfusion (arterial spin labelling) and accumulated cerebral small vessel disease (cerebral microbleeds), in COPD patients to smokers without COPD.

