This will also be the first study to explore mechanisms of cerebral small vessel disease in COPD by looking for associations between arterial stiffness, end organ vascular damage and cognitive function.

This research will provide essential data required to fund longitudinal and intervention studies designed to prevent vascular manifestations and the associated morbidity and mortality in COPD.

1. **STUDY HYPOTHESIS & OBJECTIVES**

Hypothesis:

1. COPD is associated with cerebral small vessel disease independent of smoking.
2. Cerebral small vessel disease in COPD is associated with aortic stiffness, cognitive function, cardiac, retinal & renal microvascular damage and systemic inflammation.

Objectives:

1. Test whether MRI measures of cerebral small vessel disease in COPD is independent of cigarette smoking by comparing to age and smoking history matched controls.
2. Explore possible mechanistic relationships between MR measures of cerebral small vessel disease and perfusion in COPD with pulse wave velocity and markers of systemic inflammation.
3. Determine if MRI measures of cerebral small vessel disease and perfusion are associated with measures of microvascular damage in other susceptible organs (cardiac, retina and renal) in COPD.
4. Determine if MR measures of cerebral small vessel disease and perfusion in COPD are associated with cognitive function.
5. **STUDY DESIGN**

Prospective recruitment, to an observational case control study with cross-sectional analysis designed to compare 30 well-characterised COPD cases with 25 healthy smoker controls.

The broad timetable for the stages of the research

Preparation August 2013 - Dec 2013 (4 months)

Recruitment & Data Collection Jan 2014 - Jan 2015 (12 months)

Interpreting & analysing findings Feb 2015 - March 2015 (1 month)

Preparing the final report. April 2015 - May 2015 (1 month)

*Study visits will take place at the Respiratory Research Unit, North Bristol Lung Centre.

*Retinal imaging which will take place at north Bristol medical illustration and MRI which will take place at the Clinical Research imaging Centre (CRIC) Bristol 3T MRI scanner.

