Recruitment will be from patients attending clinic at local University Teaching Hospitals. An age-matched control group will be recruited from the Bristol Primary care Research Network North Hub, local community either through local press advertisements or University non-healthcare staff. Controls will be excluded if they have any respiratory or memory difficulties.

All Participants will be invited for an MRI, retinal photography and 2 further study visits to undergo non-invasive assessment of aortic stiffness and collect the measures outlined below. The total duration of the study should be ~ 2½ hours.

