**Secondary Outcomes**

1. Aortic Stiffness: Pulse Wave Velocity
2. MRI: Number of cerebral microbleeds (CMB)
3. MRI: Cerebral perfusion (Arterial Spin Labelling – ASL)
4. Cognitive Function (Montreal Cognitive Assessment – MoCA)
5. Systemic inflammation, (C reactive protein, Interleukin 6, Fibrinogen)
6. Cardiac MR (RV, LV mass, cardiac output)
7. Micro-albuminuria
8. Retinal arteriolar narrowing (arteriole to venule ratio)
9. Forced Expiratory Volume in 1 second (FEV1 % predicted)
10. Health Status
11. Arterial partial pressure of oxygen

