**4. PARTICIPANT ENTRY**

Recruitment will be from inpatients and outpatient respiratory clinics at University Teaching Hospitals. An age-matched control group will be recruited from the local community either through local press advertisements or University non-healthcare staff. Controls will be excluded if they have any physician-diagnosed respiratory disease or self-reported memory difficulties.

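### The only recent-illness exclusion can be met by cases alone, so a case-control contrast of CRP, IL-6 and fibrinogen may be diluted by an unknown amount (minor, secondary outcome)

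*Protocol*

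**What the plan says.** Section 4.3 opens its list with "Subjects meeting any of the following criteria must not be enrolled in the study", so it formally applies to everyone. The one item in it with a look-back period for illness is "Recent exacerbation of COPD (4 weeks". The other items are standing conditions, current states or contraindications.

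Controls face further conditions. Under the control inclusion heading, "Subjects must have a FEV1/FVC >70" (per cent). Section 4 adds "Controls will be excluded if they have any physician-diagnosed respiratory disease or self-reported memory difficulties". The Study Design section words the same rule differently: "Controls will be excluded if they have any respiratory or memory difficulties". Neither version gives a time window.

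The markers at issue are secondary outcome 5, "Systemic inflammation, (C reactive protein, Interleukin 6, Fibrinogen". Their stated purpose is in Objective 2, which relates MRI measures of small vessel disease and "perfusion in COPD with pulse wave velocity and markers of systemic inflammation". Section 1.1 explains why acute episodes matter for such markers: "Acute exacerbations of COPD are inflammatory episodes associated with platelet activation, troponin rise and subsequent increased cardiovascular events".

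Blood is drawn at visit 2, after consent and history at visit 1 (section 6). No interval between the visits is given, and no check for acute illness at visit 2 is described.

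**The concern.** CRP and fibrinogen are acute-phase markers. A chest infection in a COPD patient would tend to be classed as an exacerbation and so trigger the 4-week rule. The same infection in a control triggers nothing in section 4.3. The two groups therefore enter under different stability rules for outcomes that respond to acute illness.

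If some of the 25 controls are sampled soon after an infection, the control mean and spread of the markers rise. A real excess in COPD would then look smaller than it is. The gap also touches cases: one with a recent infection that was not an exacerbation stays in, which adds variation unrelated to chronic inflammation to the associations sought in Objective 2.

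Eligibility is fixed by the Protocol. An analysis plan cannot supply a stability window that was never asked about at recruitment.

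**Working it through.** **Can a control meet the item?** It requires an exacerbation of COPD. A control has FEV1/FVC above 70% and no physician-diagnosed respiratory disease, so the answer is no.

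**Does another criterion close the gap?** The section 4 wording removes diagnosed respiratory disease; an infection that has resolved in an otherwise healthy person need not count. The Study Design wording is in the present tense and could remove someone with current symptoms, but it does not reach back 4 weeks. Non-respiratory infection is unscreened in both groups. The asymmetry is therefore mainly about respiratory infection.

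**The plan's own figure.** Section 7 gives 30 cases, 25 controls, d = 0.8, two-sided alpha 0.05, and claims power above 85%.
- Noncentrality = 0.8 / √(1/30 + 1/25) = 0.8 / 0.2708 = 2.954.
- Normal approximation: Φ(2.954 − 1.960) = 84.0%.
- Noncentral t with 53 df: 82.6%.

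The second value is the baseline below. The small shortfall against the claimed 85% is a separate matter.

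**Illustration of dilution.** The Protocol gives no infection rate, marker SD or expected marker difference, so all of these are assumed. Take a log marker with SD 1 in uninfected people and borrow the true difference of 0.8 from section 7, which is a general two-group effect and not one estimated for CRP. Let a fraction f_c of controls and f_k of cases be shifted up by s SD.
- Mean difference = 0.8 − f_c·s + f_k·s
- Variance in each group = 1 + f(1 − f)s²
- Pooled variance = (29·V_cases + 24·V_controls) / 53
- d = mean difference / pooled SD; power then follows from the noncentral t.

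Worked case, f_c = 0.08 (2 of 25), f_k = 0, s = 1: difference 0.8 − 0.08 = 0.72; control variance 1 + 0.08 × 0.92 = 1.0736; pooled variance (29 + 24 × 1.0736) / 53 = 1.0333; d = 0.72 / 1.0165 = 0.708; power 72.8%.

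| Controls affected | Cases affected | Shift (SD) | Mean difference | d | Power |
|---|---|---|---|---|---|
| 0% | 0% | – | 0.80 | 0.80 | 82.6% |
| 4% | 0% | 1 | 0.76 | 0.75 | 78.0% |
| 8% | 0% | 1 | 0.72 | 0.71 | 72.8% |
| 8% | 0% | 2 | 0.64 | 0.60 | 58.7% |
| 20% | 0% | 2 | 0.40 | 0.35 | 24.8% |
| 8% | 4% | 1 | 0.76 | 0.74 | 76.5% |
| 8% | 4% | 2 | 0.72 | 0.65 | 65.8% |
| 8% | 8% | 1 | 0.80 | 0.77 | 79.9% |
| 8% | 8% | 2 | 0.80 | 0.70 | 72.2% |

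With s = 1 and 8% of controls affected, the loss is 82.6 − 72.8 = 9.8 points if no case is affected, but 82.6 − 79.9 = 2.7 points if cases are affected equally. Most of the loss at that setting comes from the difference in rates, which the Protocol does not establish.

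**Within-COPD associations.** If 8% of cases are affected and infection is unrelated to the MRI measure, a correlation with the marker shrinks by 1/√1.0736 = 0.97 for a 1 SD shift, and by 1/√(1 + 0.0736 × 4) = 1/√1.2944 = 0.88 for a 2 SD shift.

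**The case against.** The strongest reply is that the Protocol never states a case-control comparison of these markers. Secondary outcome 5 only lists them. Hypothesis 2 and Objective 2 use them for association within COPD, and section 7 names brain pathology and vascular function for the group comparison. Control eligibility cannot affect a within-COPD association. This stands, and it limits the bias to a contrast that a study built to compare two groups would naturally report but does not spell out.

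It can also be said that controls are not unscreened. They are meant to be healthy, one of the two wordings removes anyone with respiratory difficulties, and the medical history, vital signs and full blood count could reveal a current illness. This too stands in part: it lowers the likely number of affected controls. It does not put a recent-illness window in place.

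Finally, an exacerbation criterion is disease-specific by nature, and nothing in section 4.3 is contradictory. That is fair. The point is an omission with an unequal effect, not an error of statement.

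A reader might infer that the contrast is biased towards no difference as a matter of fact. The documents do not support that. It needs recent infection to be more frequent among enrolled controls than enrolled cases, and true levels to be higher in COPD; the Protocol shows neither, and it also leaves in cases with infections that were not exacerbations.

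**Conclusion.** The point holds as a minor one on a secondary outcome. The only recent-illness exclusion binds cases alone, and no criterion covers recent infection in controls or infection other than an exacerbation in cases. A contrast of CRP, IL-6 and fibrinogen can therefore be diluted, and the associations of Objective 2 carry avoidable noise.

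The size cannot be derived from the Protocol. With only controls affected, over an assumed 4% to 20% of them and shifts of 1 to 2 SD, a true d of 0.8 falls to between 0.75 and 0.35. The upper end of that loss assumes 5 of 25 controls affected, markers still raised at sampling, and no affected case. With equal rates the mean difference is unbiased and only the variance grows.

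Two further inferences go too far. A null inflammation result would be harder to interpret, but not uninterpretable, given the history and blood count collected. And nothing here shows that the primary outcome, fractional anisotropy, is affected.

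**What to change.** Replace the disease-specific item in section 4.3 with one recent acute-illness criterion that applies to both groups: exacerbation of COPD, or any acute respiratory or other infection, within the 4-week window the Protocol already uses. Ask it at entry and again before the visit 2 blood draw, because an infection between visits 1 and 2 would affect the markers just as much. Defer an affected participant until the window has passed rather than excluding them permanently. While editing, reconcile the two wordings of the control respiratory exclusion in the Study Design section and section 4.

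The cost is a reworded line, one screening question asked twice, and an occasional delay in booking. The sample size and the primary analysis are unchanged.

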**5. ADVERSE EVENTS**

**5.1 DEFINITIONS**

**Adverse Event (AE):** any untoward medical occurrence in a patient or clinical study subject.

**Serious Adverse Event (SAE):** any untoward and unexpected medical occurrence or effect that:

- **Results in death**
- **Is life-threatening** – *refers to an event in which the subject was at risk of death at the time of the event; it does not refer to an event which hypothetically might have caused death if it were more severe*
- **Requires hospitalisation, or prolongation of existing inpatients’ hospitalisation**
- **Results in persistent or significant disability or incapacity**
- **Is a congenital anomaly or birth defect**

Medical judgement should be exercised in deciding whether an AE is serious in other situations. Important AEs that are not immediately life-threatening or do not result in death or hospitalisation but may jeopardise the subject or may require intervention to prevent one of the other outcomes listed in the definition above, should also be considered serious.

**5.3 REPORTING PROCEDURES**

All adverse events should be reported. Depending on the nature of the event the reporting procedures below should be followed. Any questions concerning adverse event reporting should be directed to the Chief Investigator in the first instance. The case report period is from time of consent until the last trial administered procedure at visit 4.

**5.3.1 Non serious AEs**

All such events, whether expected or not, will be recorded in the Case Report File (CRF)

**5.3.2 Serious AEs**

In the case of a SAE occurring, an SAE form should be completed and faxed to the trial coordination centre and to the sponsor within 24 hours. hospitalisations for elective treatment of a pre‐existing condition do not need reporting as SAEs.

All SAEs should be reported to the <name of REC> where in the opinion of the Chief Investigator, the event was:

- ‘related’, ie resulted from the administration of any of the research procedures; and
- ‘unexpected’, ie an event that is not listed in the protocol as an expected occurrence

Reports of related and unexpected SAEs should be submitted within 15 days of the Chief Investigator becoming aware of the event, using the NRES SAE form for non-IMP studies. The Chief Investigator must also notify the Sponsor of all SAEs.

Local investigators should report any SAEs as required by their Local Research Ethics Committee, Sponsor and/or Research & Development Office.

**SAE forms should be submitted by**

**[contact] attention [name]/[name]**

**Please send SAE forms to:**

**N.O.V.A.S.C study**

**Respiratory Research Unit**

**Southmead Hospital**

**Bristol**

**[name]**

**[contact] (Mon to Fri 09.00 – 17.00)**

**6. ASSESSMENT AND FOLLOW-UP**

Patients will have 4 visits. Attempts will be made to co-ordinate the study visits to suit the patient and combine them if possible / desired by the participant.

- Visit 1: Consent and collection of medical history, measures of disease severity and completion of questionnaires - much of this information will be similar to that collected in routine clinical care of patients with COPD. Lung function, health related quality of life and mood questionnaires and cognitive assessment.
- Visit 2: Non-invasive assessment of aortic stiffness, arterial blood gas and venous bloods.
- Visit 3: MRI scanning. The brain scanning protocol will last approximately 45 minutes following by a 10 minute comfort break and a further 30 minutes of cardiac scanning; resulting in a total study visit of approximately 1½ hour.
- Study Visit 4. Retinal photography. This is a short non-invasive procedure that lasts a few minutes. We anticipate the entire visit will last less than 30 minutes.

Study endpoint will be when last patient has completed last visit.

Patient withdrawal: If a patient decides to withdraw their consent during the study, then the study investigator will complete the withdrawal of consent form on the CRF. Subject to ethical approval, data already collected in relation to the participant may be retained and used for the purposes for which consent has already been given, provided they are effectively anonymised and no longer identifiable to the research team or any other persons to whom access will be given.

**7. STATISTICS AND DATA ANALYSIS**

The proposed study analysis is, informed by past empirical evidence and scientific reasoning. It is designed to investigate potentially important differences in both brain pathology, and vascular function, between COPD and Smoker groups and to investigate associations between brain pathology and vascular function. Standard statistical techniques (independent sample t-test or nonparametric Mann Whitney test as appropriate and similar) will be used. In these respects a sample size of N = 55 will be taken with N = 30 sampled from the COPD population and with a comparator group of N = 25 from a smoker population. These sample sizes have been determined on feasibility and economic grounds and are comparable with past similar research . These studies showed very large effect sizes for a two-group comparison (Cohen’s d in excess of 1.0). For a conservatively estimated effect of d = 0.8, a sample of N = 30 compared against a sample of N = 25 will have in excess of 85% power (beta < 0.10) using alpha =0.05, two-sided.

- Data and all appropriate documentation will be stored for a minimum of 10 years after the completion of the study, including the follow-up period.

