**3.1 STUDY OUTCOME MEASURES**

**Primary outcome**

MRI: White Matter microstructural damage (Fractional Anisotropy)

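### Section 7 names only unadjusted two-group tests, so the claim of a COPD effect independent of smoking rests wholly on a matching rule that is undefined and inconsistently described

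*Protocol*

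**What the plan says.** The first hypothesis, under Study Hypothesis & Objectives, is that "COPD is associated with cerebral small vessel disease independent of smoking". Objective 1 says this will be tested by comparison with controls matched on age and smoking history. The primary outcome (Section 3.1) is FA, a continuous measure.

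Matching is described in four places:

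- **Objective 1:** age and smoking history.
- **Section 4.2, controls:** "Patient and control group will be matched for smoking history and age".
- **Section 3, recruitment paragraph:** age only.
- **Section 4, opening paragraph:** age only.

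None of them gives a caliper, a pack-year tolerance or a ratio. Cases must have more than 10 pack-years. The control criteria list a spirometry threshold and no pack-year minimum. Controls are called smokers in Section 3 and ex-smokers in Section 4.2.

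On analysis, Section 7 says: "Standard statistical techniques (independent sample t-test or nonparametric Mann Whitney test as appropriate and similar) will be used". It names no covariate, stratum or matched-set term. The sample size passage compares "a sample of N = 30 compared against a sample of N = 25", at d = 0.8, "using alpha =0.05, two-sided".

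**The concern.** An independent two-sample test does not use the matching factors. How it behaves depends on how well the matching works, if age, smoking history or sex predict FA:

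- **Residual imbalance.** A remaining difference in age or pack-years passes straight into the FA contrast and is read as a COPD effect (or hides one).
- **Close matching.** The contrast is about unbiased, but variance due to the matched factors stays in the error term. The test is conservative and loses power.
- **Chance imbalance only.** The error rate is about right, but power is lower than an adjusted analysis would give.

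The matching has to carry the whole claim, and the text does not fix it firmly enough to do so. Cases come from hospital clinics, and controls from primary care, press advertisements or university staff, across ages over 40 up to 85. Balance cannot be taken for granted. Sex is neither matched nor adjusted for.

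**Working it through.** **Inputs from the protocol:** n = 30 and 25, d = 0.8, alpha 0.05 two-sided (Section 7).

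**Assumptions not in the protocol:** one composite covariate standing for age, pack-years and sex; its share of within-group FA variance, R², 0.25 with range 0.10 to 0.40; an expected group shift δ in that composite of 0, 0.33 or 0.67 SD. Total within-group SD is set to 1, and d = 0.8 is on that scale.

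**Step 1. The plan's own figure.** The scaling factor is √(30 × 25 / 55) = 3.693, so the noncentrality is 0.8 × 3.693 = 2.954. With 53 degrees of freedom (critical value 2.006), two-sided power is 82.6%; the normal approximation gives 84.0%. Neither exceeds the stated 85%, and neither gives the stated beta below 0.10. That is a separate matter, but 82.6% is the correct unadjusted baseline here.

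**Step 2. Residual imbalance, no COPD effect.** A shift δ moves the mean FA difference by √R² × δ. At R² = 0.25:

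- δ = 0.33: 0.5 × 0.33 = 0.165 SD of FA; noncentrality 0.165 × 3.693 = 0.609; rejection rate 9%.
- δ = 0.67: 0.5 × 0.67 = 0.335 SD of FA; noncentrality 0.335 × 3.693 = 1.237; rejection rate 23%.

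These biases are 0.165/0.8 = 21% and 0.335/0.8 = 42% of the effect the study is sized for.

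**Step 3. Exact balance, no COPD effect.** The true variance of the mean difference shrinks by (1 − R²), but the test's standard error does not. The rejection rate is roughly P(|Z| > 2.006/√(1 − R²)). At R² = 0.25 this is P(|Z| > 2.316), about 2.1%. Simulation, which allows for the estimated SD, gives 2.4%.

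**Step 4. Type I error across the range** (nominal 5%; Step 2 formula for the shifts, simulation with at least 20,000 data sets per scenario for the other rows and the adjusted column):

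| Setting | R² = 0.10 | R² = 0.25 | R² = 0.40 | Adjusted |
|---|---|---|---|---|
| Exact balance | about 4% | 2.4% | about 1% | about 5% |
| Chance imbalance only | 5% | 5% | 5% | about 5% |
| Expected shift 0.33 SD | 7% | 9% | 12% | about 5% |
| Expected shift 0.67 SD | 12% | 23% | 34% | about 5% |

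The shift rows average over chance variation around the expected shift. If the realised imbalance is exactly 0.33 or 0.67 SD, the rates at R² = 0.25 are about 6% and 20%.

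**Step 5. Power at d = 0.8, R² = 0.25.** Adjustment raises the effective effect size to 0.8/√0.75 = 0.924, so the noncentrality is 0.924 × 3.693 = 3.41 and power with exact balance is 92%, against 86% unadjusted (simulation). With chance imbalance only it is about 91% adjusted against 82.6% unadjusted. Adjusted power with exact balance runs from 86% (R² = 0.10) to 96% (R² = 0.40).

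**The case against.** **Matching is a legitimate control.** A reader might infer that an unadjusted test cannot address independence from smoking at all. The documents do not support that. Objective 1 says openly that smoking is handled by design, and if matching on smoking history succeeds, the unadjusted difference is not confounded by it. What stands is that this design control is undefined and inconsistently described, with no second safeguard in the analysis.

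**The error rate is not necessarily wrong.** A reader might infer that it is. It departs from 5% only if the factors predict FA and the groups are either closely balanced or systematically different. The protocol gives no figure for either. With chance imbalance only, the t-test holds its 5%.

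**A composite shift is not an age gap.** If age SD were 9 years (an assumption), 0.33 SD would be about 3 years, and a reader might attach the 9% to that gap. This holds only if age carries all the explained variance. If three independent factors contribute equally, an age-only shift moves the composite by 0.33/√3 = 0.19 SD, and the error rate is about 6.4%. For 0.67 SD of age it is 0.67/√3 = 0.39 SD and about 11%.

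**The wording is open and a SAP may exist.** Section 7 allows similar techniques, and the same paragraph covers associations that neither named test can analyse. A covariate list is also commonly left to a SAP, so its absence alone is no fault. But the protocol does name a method, and the two tests it names do not use the factors on which its design and first hypothesis depend.

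**Efficiency alone is a weak complaint.** With exact balance the unadjusted test has about 86% power, which meets the stated target. The stronger reasons to adjust are residual imbalance and power under chance imbalance.

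**Conclusion.** The point holds as a mismatch between hypothesis, design and named test on the primary outcome. Independence from smoking rests on matching alone, and the protocol does not say consistently what is matched or how closely. The consequence is conditional. If the factors explain about a quarter of FA variance, unadjusted type I error could lie anywhere from about 2.4% to 23% over the settings examined, including an unremarkable 5% when imbalance is chance only; an adjusted model stays near 5% in all of them. The power gain from adjusting is about 6 to 8 percentage points at that R². These sizes rest on an assumed R², an assumed imbalance and a covariate that acts linearly and is measured without error. They show direction and plausible scale and do not forecast this study's result.

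**What to change.** In Section 7, make the primary analysis a linear model of FA on group with age, pack-years and sex as prespecified covariates, and report the adjusted difference with its 95% confidence interval. Keep the t-test or Mann-Whitney test as a supportive unadjusted result. Use the same model for continuous secondary group contrasts.

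State the matching factors once and identically in Objective 1, Section 3, Section 4 and Section 4.2, with the tolerance for each and whether matching is by group or by individual. Reconcile the smoker and ex-smoker descriptions of the controls.

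The cost is wording and about three degrees of freedom out of 53. Pack-years must be recorded for controls as well as cases: the measures section lists a detailed medical history without naming pack-years, and the control criteria do not require them. Recalled pack-years carry measurement error, so some residual confounding by smoking can remain after adjustment, and the report should say so.

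### The power statement in Section 7 is not met by its own inputs: 30 vs 25 at d = 0.8 gives about 83% power (beta about 0.17), neither above 85% nor with beta below 0.10

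*Protocol*

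**What the plan says.** The Protocol's statistics section (Section 7) sets the total and the larger group in one sentence: "a sample size of N = 55 will be taken with N = 30 sampled from the COPD population", with 25 comparators from a smoker population. The study design text gives the same split: "designed to compare 30 well-characterised COPD cases with 25 healthy smoker controls". Section 7 says that these sizes were fixed by feasibility and cost and are similar to those of past research, in which the two-group effect exceeded d = 1.0.

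The section then gives the power of those sizes. The planning effect is introduced as "For a conservatively estimated effect of d = 0.8", the comparison is "a sample of N = 30 compared against a sample of N = 25", and the claim is that it "will have in excess of 85% power (beta < 0.10) using alpha =0.05, two-sided". The tests named for group comparisons are "independent sample t-test or nonparametric Mann Whitney test as appropriate and similar". The primary outcome, in Section 3.1, is fractional anisotropy on MRI.

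**The concern.** Every input needed to check the claim stands in Section 7, so no outside figure is required. Two things look wrong on reading. Power of 85% pairs with beta of 0.15, and beta of 0.10 pairs with power of 90%, so a reader cannot tell which target was meant. Also, 55 participants at d = 0.8 looks a little small for either figure.

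What is at stake is how a null primary result is read. Someone relying on this sentence would take the chance of missing a true difference of d = 0.8 to be under one in ten. The statement is also the only numerical support for the sample size, although not the only reason given for it.

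**Working it through.** **Inputs, all from Protocol Section 7:** n1 = 30, n2 = 25, d = 0.8 (so SD = 1), alpha = 0.05 two-sided, independent-samples t-test.

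**Stated figure:** power above 85%, beta below 0.10.

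**Exact t-test**
- Noncentrality = d × √(n1·n2/(n1+n2)) = 0.8 × √(750/55) = 0.8 × 3.693 = 2.954.
- Degrees of freedom = 30 + 25 − 2 = 53; two-sided 5% critical value = 2.006.
- Power from the noncentral t distribution = **82.6%**, so beta = 1 − 0.826 = **0.174**.

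**Normal approximation (more favourable to the plan)**
- Power = Φ(2.954 − 1.960) = Φ(0.994) = **84.0%**, so beta = **0.160**.

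**Gap to the claim**

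| | Power | Beta | Short of 85% | Short of 90% (beta 0.10) |
|---|---|---|---|---|
| Exact t-test | 82.6% | 0.174 | 2.4 points | 7.4 points |
| Normal approximation | 84.0% | 0.160 | 1.0 point | 6.0 points |

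**Attempts to recover the stated figures by changing one input**
- Equal groups of 27.5: 83.0% (t) or 84.3% (normal). Neither bound is met.
- 30 vs 30: 86.1% (t) or 87.3% (normal). This passes 85%, but beta is still above 0.10 and the group sizes are not the plan's.
- One-sided alpha 0.05 with 30 vs 25: 89.8% (t) or 90.5% (normal). This is the only variant tried that comes near beta 0.10, and the text says two-sided.

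**What would meet the bounds (exact two-sided t-test)**
- With 30 vs 25: d = 0.83 for 85% power and d = 0.89 for 90%. For reference, 80% power corresponds to d = 0.77.
- With d = 0.8 and equal groups: 30 per group for 85% and 34 per group for 90%.

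**At the effect size attributed to past studies:** with 30 vs 25 and d = 1.0, power is 95.2% (beta 0.048).

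**The case against.** The best defence is that little turns on the error. The sample size was fixed by feasibility and cost, and the power figure describes it rather than produced it. Power at the planning effect is still above 80%, and at d = 1.0, which the cited studies are said to exceed, it is 95.2%. Under the normal approximation the 85% claim misses by only one point. All of this stands. It limits the weight of the finding but does not make the sentence correct.

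Three stronger readings are tempting, and the Protocol does not support them.

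- **That the sentence contradicts itself.** A power of 92% would satisfy both bounds, so the two thresholds fail to correspond but are not logically incompatible. The fault is that neither is met.
- **That the sample size loses its only justification.** Section 7 also gives feasibility, cost and comparability with earlier work. What is affected is the only quantitative support.
- **That true power is lower still.** A reader might cite lost scans, the permitted Mann-Whitney test, or effects of d = 0.5 or 0.6. The Protocol gives no scan-loss rate. The usual efficiency of 0.955 for Mann-Whitney (about 80.8% power here) holds for normal data, whereas the plan reserves that test for when it is appropriate. The Protocol makes no power claim at smaller effects. Any of these could be shown as a labelled assumption, but none is part of the error.

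**Conclusion.** The statement is wrong as written. For d = 0.8, 30 vs 25 and two-sided alpha 0.05, power is about 83% and beta about 0.17. The power half is a modest overstatement. The beta half is the substantive error: the true value is about 1.7 times the stated ceiling (0.174/0.10). A one-sided calculation may explain where it came from, but that is conjecture and conflicts with the stated two-sided alpha.

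The result assumes the named t-test, normal data with equal variances, and 30 and 25 participants with usable primary data. The 17% is the false-negative risk only if the true effect is d = 0.8. A reader might go on to infer that the study is underpowered or must be enlarged. The figures do not show that, since power at the plan's own effect size stays above 80%.

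**What to change.** In Section 7, delete the beta figure and replace the power sentence with wording such as:

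> With 30 and 25 evaluable participants, a two-sided t-test at the 5% level has about 83% power (beta about 0.17) for d = 0.8; the effect detectable with 80% power is d = 0.77 and with 90% power d = 0.89.

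The cost is one sentence and a slightly less favourable figure. Group sizes, outcomes and analysis are unchanged. If the authors also want to show power under lost scans or a rank test, they should give it as a sensitivity figure with its assumption stated; the correction does not require it.
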